### Secondary outcome measures

Subscales of the DASS-21 (symptoms of depression, anxiety, stress individually) will be secondary outcomes. The 8-item Patient Health Questionnaire (PHQ-8) will be used as a screening measure to screen for low mood and will be administered fortnightly to measure changes in the severity of low mood. The PHQ-8 will also be used to measure changes in mood to detect any untoward changes in the severity of low mood throughout participants’ involvement in the trial.

Cognitive performance will be measured by a validated computerised cognitive brief battery, which has been used extensively in clinical trials, developed by Cogstate (Cogstate Ltd., Melbourne, Australia). The four tasks comprising the Cogstate Brief battery, from which main outcome variables will be analysed: Working Memory (One Back); Visual Learning (One Card); Psychomotor Function (Detection); and Attention (Identification). Additionally, the Paired Associate Learning (Continuous Paired Associate Learning) will be used as a measure of memory processes relating to encoding and retrieval [45, 46]. Both measures have acceptable construct and criterion validity in a neuropsychological context [47].

The World Health Organization (WHO) WellBeing Index will be utilised to assess perceived wellbeing. Each statement is rated on a Likert scale (0–5) to assess how applicable they are to the participant’s feelings in the past 14 days. The total score indicates the level of wellbeing, which may range from an absence to maximal wellbeing [48].

The Athens Insomnia Scale will be utilised to assess sleep difficulty, quality and duration in the past month. It is an eight-item self-assessed psychometric instrument based on the WHO’s International Statistical Classification of Diseases and Related Health Problems (ICD-10) criteria [49].

Psychosocial aspects of quality of life will be assessed utilising the Assessment of Quality of Life (AQoL)-8D, a Multi-Attribute Utility instrument developed by Monash University [49]. The instrument contains 35 items, which load onto eight dimensions. Three of these are related to a physical super-dimension (independent living, pain, senses) and the remaining five to a psychosocial super-dimension (mental health, happiness, coping, relationships and self-worth). The 35 items may be reduced to a single utility score using the AQoL-8D algorithm, to reflect health-related wellbeing [49]. The utility values will also be used to calculate quality-adjusted life years (QALYs), a standard outcome measure in economic evaluations.

To determine participants’ broader use of healthcare services, a Resource Use Questionnaire (RUQ) will be completed at weeks 0 and 16. An economic evaluation will be undertaken as a cost consequences analysis from a primarily health sector perspective with an additional partial societal perspective included. The evaluation will measure and value the use of health care resources over the trial period for those in the intervention and control groups, and then compare any additional costs to the primary and secondary outcomes including QALYs. Medical resources collected through the RUQ will be costed using standard Australian unit costs (i.e. Medicare Benefits Schedule and Pharmaceutical Benefits Scheme). Lost work productivity, also captured in the RUQ, will be costed using the human capital approach by applying an average hourly wage rate plus 25% overhead costs [50, 51].

Functional GI disorders (e.g. irritable bowel syndrome, constipation, diarrhoea, and abdominal pain) will be assessed using the Rome IV Bowel Disorders and Central Nervous System Disorders of Gastrointestinal Pain Module, a sub-module of The Rome IV Diagnostic Questionnaire for Functional Gastrointestinal Disorders in Adults (R4DQ). This module contains questions from the R4DQ (Q: 40-67) and will be used to assess GI disorders in participants [52]. The Visual Analogue Scale for Irritable Bowel Syndrome (VAS-IBS) questionnaire is a valid self-imaging tool that measure changes in GI symptoms in patients with IBS [53]. This tool will be used to capture changes in gut symptomology (e.g. bloating, abdominal pain) in the intervention and control groups every fortnight. Participant’s stool formation will be assessed using the Bristol Stool Form Scale (BSFS) questionnaire every fortnight [54].

The gut microbiota composition will be assessed via stool samples using 16S rRNA gene sequencing. This technique is extensively used in identification of bacterial taxa in both animal and human faecal samples [55]. After sequencing, the 16S rRNA gene sequences will be matched to reference databases to identify operational taxonomic units corresponding to the genus or species level. In addition, subject to funding, stool samples may be sent for metagenomics analysis, an advanced and more in-depth analysis technique for assessing microbiota composition and inferred function [56].

Biomarkers of immune function and oxidative stress will be assessed via blood samples collected from participants. Markers of immune function (tumour necrosis factor-α, interleukin (IL)-1β, IL-6, IL-10) and gut inflammation (IL-4, humoral immune markers: immunoglobulin E, immunoglobulin G) will be analysed [57, 58]. Markers of endothelial integrity such as liposaccharide-binding protein (LBP) and CD14, which are indicators of microbial product dissemination to the peripheral circulation, will also be assessed [59, 60]. Changes in oxidative stress levels will be assessed using GSH, a marker of cellular redox balance [61]. Moreover, changes in metabolomic markers such as short-chain fatty acids (SCFA) and BCM-7 will be assessed. SCFA are metabolic by-products of microbial fermentation of dietary fibre in the gut and serve as markers of colonic health [62]. This study will measure SCFA concentrations in stool samples collected from participants, subject to funding. BCM-7 that are yielded by the enzymatic digestion of A1 beta-casein protein in milk will be measured in blood samples [61].

A whole body scan will be carried out using the dual energy X-ray absorptiometry (DXA, Lunar Prodigy Pro) to study body composition, which indicates fat, lean and bone mass of the participants [63].

Data will also be collected related to participant demographics, habitual diet using the Cancer Council’s Dietary Questionnaire for Epidemiological Studies v3.2 (DQES) [64], physical activity using the short form of the International Physical Activity Questionnaire (IPAQ) [65] and symptoms of personality disorders using the Standardised Assessment of Personality Abbreviated Scale (SAPAS) [66]. These variables will be examined as potential effect modifiers in exploratory post hoc subgroup analyses.

### Adverse events

Adverse events (AE) will be monitored and recorded at all timepoints, which will be overseen by the study management team. Any unfavourable or unintended medical occurrence (e.g. sign, symptom, syndrome and illness) that develops or worsens during the trial will be reported as an AE. All AEs will be assessed for severity (mild, moderate, severe), causality (not related, unlikely, possibly, probably or definitely related to study treatment) and seriousness and will be documented by the study team. For any AE (regardless of seriousness or severity), researchers will maintain contact with participants until it has been resolved and symptoms disappear. If a participant experiences a significant AE, they may be withdrawn from the study. The decision will rest with the principal investigator and the participant will be referred to their treating doctor, if required. In the case of a serious adverse event (SAE), the HREC will be notified within 24 h of the researchers becoming aware of the event. Emergency unblinding will occur for an SAE deemed related to the study product.

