#### Intervention period

Within 2 weeks of commencing the intervention, a study member will contact participants by phone to discuss adherence, trouble-shoot any difficulties encountered during the study period and book additional study visits. In between clinical assessments, participants will complete online fortnightly self-report questionnaires and a weekly adherence questionnaire (see Table 2). The final (week 16) self-report questionnaires will be emailed to participants to complete online, to reduce burden and minimise time spent in-clinic.

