### Statistical methods

All randomised participants with valid 0 and 16-week observations will be included in the primary analysis (modified intent-to-treat analysis). The primary outcome will be analysed using generalised estimating equation (GEE), using an identity link function and normal distribution, to test the between-group differential change in DASS-21 total score from baseline to 16 weeks follow-up between the intervention and control groups. This will be estimated through two-way interaction between group allocation and follow-up time points in a GEE model that includes nominal intervention allocation factor, nominal measurement time and the two-way interaction between allocation and measurement time. In order to account for within-participants’ autocorrelation due to repeated measurements, Huber/White cluster sandwich variance estimates will be used to account for clustering from the same study participants [72]. As a secondary analysis, an additional GEE model will be implemented that includes all observations with at least one post-baseline measure. All other secondary longitudinal continuous outcome analyses will follow the same method as the primary outcome analysis. Sensitivity analysis may be used to evaluate missing at random assumptions for missing follow-up data. This will be done by imputing data assuming missingness is positively or negatively associated with outcomes in the intervention and control group and then the intervention effect sizes will be estimated from these different imputation scenarios. An additional sensitivity analysis will be performed with a GEE model adjusted for baseline measurements as potential covariates. Exploratory post hoc subgroup analyses may also be conducted if feasible to explore possible moderation of intervention effects (e.g. menopause status). Cross-sectional associations of baseline demographic and prognostic variables (e.g. habitual diet, exercise, personality, biomarkers) will also be explored. This work will be independent to the main trial report and will be conducted subject to further funding and staff resourcing.

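### Withdrawal from the study after a significant adverse event, combined with a primary analysis limited to women with a week-16 score, can make exclusion depend on the outcome itself

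*Protocol article*

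**What the plan says.** Four parts of the protocol article bear on this.

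- **Adverse events, definition.** "Any unfavourable or unintended medical occurrence (e.g. sign, symptom, syndrome and illness) that develops or worsens during the trial will be reported as an AE". Mood is not exempted.
- **Adverse events, consequence.** "If a participant experiences a significant AE, they may be withdrawn from the study". The article does not define significant, which is not one of the terms on which the section grades events (severity, causality, seriousness). On who decides: "The decision will rest with the principal investigator and the participant will be referred to their treating doctor, if required". For any adverse event, "researchers will maintain contact with participants until it has been resolved and symptoms disappear"; the section does not mention collecting outcomes after withdrawal.
- **Secondary outcome measures.** The PHQ-8 is given fortnightly, in part "to detect any untoward changes in the severity of low mood".
- **Statistical methods.** "All randomised participants with valid 0 and 16-week observations will be included in the primary analysis (modified intent-to-treat analysis"). A secondary GEE model takes in women with at least one post-baseline measure. A sensitivity analysis that imputes missing scores under different assumptions is optional.

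On collection, the Intervention period section says: "The final (week 16) self-report questionnaires will be emailed to participants to complete online".

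**The concern.** The primary outcome is the change in DASS-21 total score from baseline to week 16, in women enrolled for low mood. If a woman's mood worsens, the fortnightly PHQ-8 can show it, the event can be recorded as adverse, and the investigator may withdraw her from the study. She would then normally have no week-16 DASS-21 and would not enter the primary analysis, although she was randomised. Her exclusion would follow from a poor value of the construct being compared.

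What is at stake is the size of the primary estimate. The hypothesis is lower distress on A2 dairy than on conventional dairy. If that is true, more control than A2 women would cross any common threshold for concern. Removing them makes the remaining control group look better and the contrast smaller.

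**Working it through.** **The plan's own figures.** From Power calculation: difference 2.3 points, SD of change 3.6, two-sided 0.05, 80% power, 40 per arm.

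- Normal approximation: n per arm = 2 × (1.96 + 0.84)² × (3.6/2.3)² = 38.4, so 39. The t-test version gives 39.4, so 40. The stated 80 is reproduced.
- 80 × 1.125 = 90, the stated number to randomise. The sample size is not in dispute; 2.3 and 3.6 serve only as yardsticks below.

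**Size of the shift.** Let p be the proportion of an arm withdrawn and e the number of points by which those women would have ended worse than completers in the same arm.

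- All-randomised mean = completer mean + p × e, in each arm.
- Shift of the completer difference towards zero = (p control − p A2) × e, taking e as equal in both arms.

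The article gives neither p nor e. Assumed ranges: control 8–12%, A2 4–5%, e 4–8 points.

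| Case | Calculation | Shift (points) | Share of 2.3 |
|---|---|---|---|
| Smallest | (0.08 − 0.05) × 4 | 0.12 | 5% |
| Middle | (0.10 − 0.05) × 6 | 0.30 | 13% |
| Largest | (0.12 − 0.04) × 8 | 0.64 | 28% |

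**Cross-check with a common threshold.** Assume change is normal with SD 3.6, mean 0 in control and −2.3 in A2, and that women who worsen beyond one cut-off, the same in both arms, have no week-16 score.

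| Control lost | A2 lost | Completer difference | Attenuation if all beyond the cut-off are withdrawn | Attenuation if half are |
|---|---|---|---|---|
| 5% | 1.1% | −2.02 | 12% | 6% |
| 10% | 2.7% | −1.83 | 20% | 9% |
| 12.5% | 3.7% | −1.75 | 24% | 11% |
| 20% | 6.9% | −1.56 | 32% | 14% |

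The first three columns are for withdrawal of everyone beyond the cut-off. Simulated power with 45 randomised per arm is about 85% with no loss, and about 80%, 73% and 62% at control losses of 5%, 10% and 20%. That fall includes the effect of fewer women as well as the shift. The model ties withdrawal to the final change score itself, the most direct form of dependence.

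**Direction.** With no true effect and equal withdrawal, p control = p A2 and the shift is zero. Withdrawal that is unequal for other reasons could move the estimate either way.

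**The case against.** The strongest reply is that the chain is partly inferred. No sentence says that worsening mood is an adverse event, and none ties a PHQ-8 or DASS-21 score to withdrawal. Table 2 lists self-reported health and adverse effects in a separate row from both scales. Withdrawal is discretionary, and the Blinding section keeps investigators blind to allocation. All of this stands. A reader might infer that the plan classes worsening mood as an adverse event and removes such women as a rule. The text does not support that; it supports only that the stated rules permit it. Blinding prevents deliberate differences between arms, but it does not stop one common threshold from catching more women in the arm that does worse.

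Second, withdrawal is not shown to end data collection. Contact continues until the event resolves, and the primary analysis would accept a withdrawn woman who has a week-16 score. This also stands, and it is why the remedy concerns collection. But contact until resolution is not a commitment to collect the DASS-21 at week 16, and the wording is withdrawal from the study.

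Third, there are safeguards. The secondary GEE uses scores recorded before withdrawal, and the optional sensitivity analysis addresses missingness related to outcome. A reader might infer that missing-at-random methods are of no use here. That goes too far: withdrawal prompted by recorded fortnightly scores depends partly on observed data. Still, one safeguard is secondary, the other is optional, and a GEE without weighting or imputation is not generally valid when dropout depends on earlier outcomes.

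Fourth, the assumed rates may be high. They average 6% ((8 + 4)/2) to 8.5% ((12 + 5)/2) across arms, about half to two-thirds of the 12.5% total attrition planned for. Control women also already drank conventional milk, so they are not newly exposed to A1. Both remarks argue for the lower end of the range. The middle case, 0.30 points, is small against a standard error of 3.6 × √(2/40) = 0.80.

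**Conclusion.** The point holds as a possibility that the stated rules create, not as a demonstrated bias. Three statements combine: withdrawal is from the study, the adverse event definition is wide enough to include worsening mood, and the primary set requires a week-16 score. Together they allow exclusion to depend on the outcome.

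Under the assumed rates, the shift is 0.12–0.64 points, 5–28% of the 2.3-point target. The common-threshold model gives 12–24% attenuation when 5–12.5% of control women are lost, and 6–11% if only half of those beyond the cut-off are withdrawn. These figures rest on withdrawal rates and excess worsening that the article does not give. The attenuation also requires a true A2 benefit. A reader might infer that the primary result is bound to be biased, or that a null result would be explained by this; the documents support neither. The change is worth making because it is cheap and protects the primary result, which the planned secondary and optional analyses do not.

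**What to change.** In the Adverse events section, distinguish a participant who stops study product from one who withdraws from follow-up. Who stops product, and why, stays exactly as it is. State that the online DASS-21, at least at week 16, continues to be emailed to every randomised woman who has not withdrawn consent. Her score then enters the primary analysis in her allocated arm. The Statistical methods rule already admits any randomised woman with both scores, so the gain comes from collecting the score.

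The cost is a protocol sentence, a check of the consent wording and one short form for a few women. The week-16 questionnaires are already emailed and completed online. The Trial status section reports a pause and foresees amendments before recruitment resumes, so the change can be made then.

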### Power calculation

To date, no studies have investigated the effects of A2 beta-casein only vs conventional dairy products on symptoms of psychological distress. For this reason, the anticipated effect size is largely based on findings derived from the broader nutrition literature [67–71]. A feasible sample size of 80 participants (40 per study arm) has been calculated to detect a medium intervention effect size of 0.63 (standard mean differences) defined as a between-group standard mean difference in DASS-21 total score from baseline to 16 weeks between the intervention and control groups. We assume the standard deviation of DASS-21 score change is 3.6, which is similar to published RCTs [67–69]. A sample size of 80 participants, achieves 80% power for a two-tailed analysis with a type I error level of 0.05 to detect a between-group mean difference of 2.3 or greater in DASS-21 total score from baseline to 16 weeks between the intervention and control groups. The total sample size will be inflated to 90 to account for an anticipated attrition rate of 12.5%. If our attrition rate is higher than anticipated (e.g. due to COVID-19 pandemic), we will aim to recruit further participants.

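### Randomising 90 women keeps 80 completers only up to 11.1% attrition, not the stated 12.5%; the loss of power is negligible, but the figure and the recruitment trigger tied to it should be corrected

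*Protocol article*

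**What the plan says.** The Power calculation section of the protocol article sets the number to be analysed first: "A feasible sample size of 80 participants (40 per study arm) has been calculated to detect a medium intervention effect size of 0.63". The inputs on the raw scale follow: "We assume the standard deviation of DASS-21 score change is 3.6", and the target is a difference between the arms of at least 2.3 points. For that target, the section says that the chosen number "achieves 80% power for a two-tailed analysis with a type I error level of 0.05". The total is then raised for loss to follow-up: "The total sample size will be inflated to 90 to account for an anticipated attrition rate of 12.5" per cent. The same section adds that further women will be sought if attrition proves higher than anticipated. The abstract and the section on eligibility and recruitment also give ninety women.

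The Statistical methods section limits the primary analysis to randomised women with valid observations at week 0 and week 16. A second model that keeps anyone with at least one post-baseline measure is a secondary analysis.

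**The concern.** An attrition rate is a fraction of those randomised. To keep a given number of completers, that number is divided by one minus the rate. Multiplying by one plus the rate gives a total that is slightly too small. The 90 looks like the result of the multiplication, in which case the trial does not keep its own 80 completers at its own anticipated attrition.

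Two things depend on this. The primary set consists of women with both baseline and week 16 data, so each woman lost by week 16 leaves the primary analysis, and the number of completers is the number that carries the power statement. The anticipated rate also serves as the threshold above which extra women are recruited. If 90 does not cover 12.5%, that threshold is too high to protect 80 completers.

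**Working it through.** **Inputs** (Power calculation section unless noted): 80 women needed, 40 per arm; difference 2.3 points; SD of change 3.6; two-sided type I error 0.05; power 80%; anticipated attrition 12.5%; total 90; allocation 1:1 (Trial design and setting).

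**Step 1. Reproduce the 80.** For a comparison of two means, the expected test statistic is difference / (SD × √(1/n₁ + 1/n₂)). With 40 per arm this is 2.3 / (3.6 × √(2/40)) = 2.3 / 0.805 = 2.857. Power is Φ(2.857 − 1.960) = 81.5% by normal approximation and 80.6% by noncentral t. The smallest number per arm that reaches 80% is 39 (normal) or 40 (t). The plan's 80 reproduces.

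**Step 2. Reproduce the 90.** 80 × (1 + 0.125) = 90 exactly.

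**Step 3. Apply the stated attrition to 90.**
- Expected completers: 90 × (1 − 0.125) = 78.75, about 79.
- Attrition that leaves exactly 80 of 90: (90 − 80)/90 = 11.1%.
- Total that keeps 80 at 12.5%: 80/(1 − 0.125) = 91.43, so 92 (46 per arm), with 92 × 0.875 = 80.5 expected completers.

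**Step 4. Power at the number expected to complete** (2.3 points, SD 3.6, two-sided 0.05). For 79 completers split 39 and 40: 2.3 / (3.6 × √(1/39 + 1/40)) = 2.3 / 0.810 = 2.839.

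| Completers | t test | Normal approximation |
|---|---|---|
| 80 (40/40) | 80.6% | 81.5% |
| 79 (39/40) | 80.05% | 81.0% |
| 78 (39/39) | 79.5% | 80.5% |

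Each completer lost costs about half a percentage point.

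**Step 5. The recruitment trigger.** With 90 randomised, 10 losses are 11.1% and leave 80. Eleven losses are 11/90 = 12.2% and leave 79, which is below 80 but still under 12.5%, so the trigger does not act. Twelve losses are 12/90 = 13.3% and leave 78, and it acts. At 90 randomised, the trigger is late by one woman.

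**Step 6. Is the effect size of 0.63 consistent with the rest?** The smallest standardised difference detectable with 40 per arm at 80% power is 0.634 (t) or 0.626 (normal). Both round to 0.63. Multiplied by 3.6 they give 2.28 and 2.26, and both round to 2.3. The printed 80, 0.63, 3.6 and 2.3 fit one calculation reported to limited precision.

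**The case against.** The strongest reply is that nothing of substance is lost. The gap is two women at randomisation, or about one completer. The power sentence for 2.3 points does not strictly need 80 completers, since 79 still reach 80% by either method. The SD of 3.6 is itself only described as similar to published trials; an SD of 3.7 would lower power at 40 per arm by about 2 points, more than the whole effect of the slip. All of this stands, and it sets the weight of the point.

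It might also be said that the promise to recruit more women covers any shortfall. It does not, because it applies only when attrition exceeds the anticipated rate and the shortfall arises at that rate. The secondary model that keeps partial data does not help either, because it is not the primary analysis.

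A reader might infer two stronger points that the document does not support:

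- **That the trial is underpowered as planned.** This comes from taking 78 completers and a t test together, which gives 79.5%. The expectation is 78.75, nearer 79, where power is 80.05% by t test and 81.0% by normal approximation.
- **That the effect size is inconsistent and 41 per arm are needed.** Dividing 2.3 by 3.6 gives 0.639, and treating 0.63 as exact in a t test gives 79.5% at 40 per arm. But 0.63 is the correctly rounded detectable effect under both methods (step 6). By normal approximation 40 per arm at 0.63 gives 80.4%. The section names no test, and the planned analysis is a generalised estimating equation. The difference is rounding.

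**Conclusion.** The statement that 90 accounts for 12.5% attrition from 80 is wrong as written. Ninety covers 11.1%; at 12.5% about 79 women are expected to complete, and keeping 80 would take 92. The error is minor. Power for 2.3 points stays at about 80%, some half a point below its value at 80 completers, and no conclusion of the trial turns on it. It merits correction because the figure justifies the total and also sets when extra recruitment begins.

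The result assumes that attrition means absence from the primary set, that losses are about equal in the two arms, and that a two-sample comparison of change with SD 3.6 represents the primary contrast, as the power calculation itself does.

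**What to change.** Either of two restatements in the Power calculation section is enough:

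- 90 randomised keeps 80 completers with attrition up to 11.1%; or
- at 12.5% attrition about 79 of 90 complete, with about 80% power for 2.3 points and SD 3.6.

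In the same section, tie the trigger for recruiting further women to attrition above 11.1%, or more simply to fewer than 80 expected completers, in place of 12.5%. The second wording still works if the number randomised changes.

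Leave the effect size of 0.63 as it is.

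The cost is a change of wording with no extra participants. Recruitment was halted and is due to resume, and the Trial status section already foresees amendments, so the correction can be made along with them. Raising the total to 92 would also remove the mismatch, but the power at stake does not require it.
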